## Abstract

**Background:**

South Africa is among the seven highest tuberculosis (TB) burden countries. Harmful lifestyle behaviours, such as smoking and alcohol, and poor adherence to medication can affect clinical outcomes. Modification of these behaviours is likely to improve TB treatment outcomes and has proven possible using motivational interviewing (MI) techniques or use of short message service (SMS) text messaging. There have been no studies assessing the effect of combined MI and SMS interventions on multiple lifestyle factors and TB treatment outcomes.

**Methods:**

This is a prospective, multicentre, two-arm individual randomised controlled trial looking at the effectiveness and cost-effectiveness of a complex behavioural intervention (the ProLife programme) on improving TB and lifestyle-related outcomes in three provinces of South Africa. The ProLife programme consists of an MI counselling strategy, delivered by lay health workers, augmented with subsequent SMS. We aim to recruit 696 adult participants (aged 18 years and over) with drug-sensitive pulmonary TB who are current smokers and/or report harmful or hazardous alcohol use. Patients will be consecutively enrolled at 27 clinics in three different health districts in South Africa. Participants randomised individually to the intervention arm will receive three MI counselling sessions one month apart. Each MI session will be followed by twice-weekly SMS messages targeting treatment adherence, alcohol use and tobacco smoking, as appropriate. We will assess the effect on TB treatment success, using standard World Health Organization (WHO) treatment outcome definitions (primary outcome), as well as on a range of secondary outcomes including smoking cessation, reduction in alcohol use, and TB medication and anti-retroviral therapy adherence. Secondary outcomes will be measured at the three-month and six-month follow-ups.

**Discussion:**

This trial aligns with the WHO agenda of integrating TB care with the care for chronic diseases of lifestyle, such as provision of smoking cessation treatments, and with the use of digital technologies. If the ProLife programme is found to be effective and cost-effective, the programme could have significant implications for TB treatment globally and could be successfully implemented in a wide range of TB treatment settings.

**Trial registration:**

ISRCTN Registry, ISRCTN62728852. Registered on 13 April 2018.

**Electronic supplementary material:**

The online version of this article (10.1186/s13063-019-3551-9) contains supplementary material, which is available to authorized users.

## Background

South Africa has the second highest incidence of tuberculosis (TB) and the sixth highest TB burden of the 30 high TB burden countries. It also has a high prevalence of human immunodeficiency virus (HIV) co-infection in patients with TB and a high mortality in these co-infected patients relative to most other high-burden countries [1]. In addition to HIV co-infection, a range of social, psychological and economic factors influence treatment success in TB. Of these, tobacco smoking and hazardous or harmful alcohol use are specifically mentioned in the South Africa National TB Management Guidelines [2]. Tobacco use and problem drinking are prevalent in TB patients, often co-occur [3–5] and are known to increase the risk of death and poor treatment adherence and outcomes [6–9].

As well as increasing the risk of TB infection and progression of disease [10], smoking is also known to increase the risk of treatment failure [11], relapse [12, 13] and death [14], and is associated with resistance to isoniazid, one of the main antimicrobials used to treat TB [15]. There is evidence that patients who stop smoking have better TB treatment outcomes and, if co-infected, better HIV treatment outcomes than current smokers [16–18]. In addition, alcohol misuse is associated with poorer TB outcomes through a range of mechanisms including decreased effectiveness of medications used to treat TB (including drug resistance), increased recurrence and treatment default rates and social marginalisation [3]. It has been estimated that 10% of the global burden of TB is attributable to alcohol use [19, 20].

Poor adherence to TB medication and anti-retroviral therapy (ART) significantly increases the risk of adverse effects and death in TB patients. Strategies are needed to improve medication adherence in TB-HIV co-infected patients, in whom integration of TB and HIV care has been shown to decrease mortality [21].

A number of studies have attempted to evaluate the effectiveness of tobacco cessation, alcohol reduction or TB treatment adherence interventions in TB patients [21, 22], but few have assessed the effect on TB treatment outcomes [23, 24]. We know that brief smoking cessation interventions, ranging from opportunistic advice and proactive telephone support through to in-person behavioural support over multiple sessions, are effective and affordable in low-income countries, in both TB patients and smokers in the general population [25, 26]. We also know that disease diagnosis could constitute a ‘teachable moment’, when people are more amenable to advice and motivated to modify harmful lifestyle behaviours [27]. For this reason, it is likely that patients receiving a TB diagnosis may be more successful in quitting smoking and moderating alcohol use if offered behavioural support, compared with smokers and problem drinkers in the general population.

Motivational interviewing (MI) is a counselling technique known to facilitate behaviour change [28], which has demonstrated effectiveness for the reduction of hazardous drinking, tobacco cessation, and TB treatment and/or ART adherence [19, 29, 30]. Our group has had previous success in achieving sustained smoking abstinence in TB patients through a brief MI intervention delivered by lay health workers (LHWs) [31]. There is also evidence to suggest that adherence to ART [32] and possibly TB medication [33], as well as tobacco cessation, can be enhanced with the use of short message service (SMS) text messages on mobile phone technology [34]. To our knowledge, no study has used MI in combination with SMS text messages to address multiple harmful behaviours that adversely impact TB outcomes.

The ProLife programme is a novel complex behavioural intervention targeting tobacco smoking, problem drinking, and TB and HIV medication adherence in patients with TB. This is the study protocol for the randomised controlled trial (RCT) aiming to assess the effectiveness and cost-effectiveness of the ProLife programme in improving TB treatment outcomes in primary healthcare clinics located in high TB-burden communities in three provinces in South Africa (Gauteng, Free State and North West). The protocol has been written in accordance with the Standard Protocol Items: Recommendations for Intervention Trials (SPIRIT) guideline.

## Methods/Design

### Objectives

The primary objective is to assess the effectiveness and cost-effectiveness of the ProLife programme compared to usual care in improving pulmonary TB (PTB) treatment outcomes. We also aim to assess the effectiveness and cost-effectiveness of the programme in achieving abstinence from smoking, reducing harmful and hazardous drinking, and improving TB and ART medication adherence.

### Trial design and setting

This is a pragmatic, prospective, multicentre, two-arm, parallel, individual RCT taking place in 27 purposively selected primary care clinics with the highest TB case-load in three districts in South Africa: Welkom in the Free State; Bojanala in the North West province; and Sedibeng in Gauteng province. To be eligible for inclusion in the trial, TB clinics had to be under the control of the provincial or local government (i.e. not a mining TB clinic). The intervention will be delivered by LHWs and three district coordinators who will each cover 1–2 clinics.

Participants will be randomly allocated to one of two arms:Arm 1: Intervention arm – participants in the interventions arm will receive the ProLife programme;Arm 2: Control arm – participants will receive usual treatment and support provided to TB patients in TB treatment clinics in South Africa (‘usual care’).

### Intervention

The ProLife programme is a complex behavioural intervention aimed at improving treatment outcomes in TB patients who smoke tobacco, drink alcohol at harmful or hazardous levels, or do both. The ProLife programme has been developed in line with the Medical Research Council (MRC) guidance on developing and evaluating complex interventions [35] and has undergone a period of development and feasibility testing in South Africa. The paper reporting the results of this evaluation has not yet been published. The conceptual framework used to develop the ProLife programme assumes that smoking cessation, reducing harmful alcohol use and improved adherence to TB and HIV treatment will result in improved TB treatment outcomes.

Participants randomised to the intervention arm will receive three brief MI counselling sessions, lasting 15–20 min, each one month apart, from a trained LHW at their TB clinic. In the initial MI session, occurring at the start of TB treatment, the counsellor will establish the participant’s tobacco smoking habits and problem drinking; potential obstacles and facilitators for medication adherence or treatment initiation (both TB treatment and ART) will be determined. The participant will determine which factor should be prioritised (i.e. agenda setting), which could be a plan either to quit tobacco smoking, reduce or quit drinking or deal with barriers relating to ART or TB medication adherence. For participants who are HIV-infected and not yet on ART, beliefs and attitudes regarding HIV-testing or ART will be explored to facilitate ART initiation and adherence. The second session will build on the previous one and will focus on the previous agenda before moving on to the next behavioural problem (tobacco, alcohol or medication adherence) where applicable. The third session will deal with the last identified problem.

The individual counselling sessions will be re-enforced with SMS text messages regarding information, motivation and behaviours (IMB) supporting tobacco cessation, alcohol use and medication adherence. Text messages will be delivered twice a week over 12 weeks. All participants will first receive 10 TB-related messages. These messages will be followed by seven alcohol or smoking-related messages depending on whether the participant smokes or drinks. Co-joint users will receive all sets of messages (i.e. 24 in total).

### Comparator

Participants in the second group are the controls and will receive usual TB treatment and support offered to TB patients. Control participants are seen by a TB nurse and receive the same biochemical investigations and medical treatments as the intervention arm. However, they will not receive the MI and SMS package of care as described above. Usual care also includes HIV testing with pre- and post-test HIV test counselling by a lay counsellor or a nurse (this varies by district).

In addition, health education is given on:nature of TB, treatment adherence, treatment side-effects/complications, drug interactions, tobacco use, alcohol use and other substance abuse. This is mostly done by the TB nurses, is not intensive and is educational in nature rather than a form of counselling;healthy diet by a dietician where possible;social problems and family support for treatment by a social worker as needed and depending on the availability of social workers; andpoint of care blood glucose, haemoglobin and pregnancy tests are performed. If co-infected with HIV, a full blood count, liver function test and creatinine are also carried out.

### Participants

The inclusion criteria for participants are:adult patients (aged ≥ 18 years) with drug-sensitive (bacteriologically or clinically confirmed) PTB;initiating TB treatment or on TB treatment for < 1 month (these include both ‘new’ and ‘retreatment’ patients);current smokers and/or hazardous/harmful drinkers who are not alcohol dependent (Alcohol Use Disorders Identification Test [AUDIT] score ≥ 8 for men or ≥ 7 for women but < 20);access to a functional mobile phone; andunderstands one of the four languages used for the trial (Sesotho, Setswana, Isizulu or English).

Exclusion criteria:alcohol-dependent participants (AUDIT score ≥ 20);Extrapulmonary TB without PTB; orResistance to one or more TB drugs at baseline (because drug-resistant TB needs further investigations which take several months and is treated through a long, specialised treatment programme if present).

### Recruitment process

Participants will be recruited consecutively from the starting date of the trial until the required sample size for each clinic has been achieved. The sample size per clinic will vary depending on the workload for each clinic. TB patients who initiate treatment (or who have been on treatment for < 1 month) will be asked if they would like to participate. If they agree, they will then be screened for eligibility by trained fieldworkers immediately after the TB nurse at the clinic has initiated TB treatment and started the routinely used TB treatment record. Eligibility screening will involve being assessed in line with the inclusion criteria listed above and being asked about their:smoking status: using the Global Adult Tobacco Survey [36] questionnaire, patients will be asked whether they currently smoke daily, less than daily or not at all, and in the past daily, less than daily or not at all. As TB patients in South Africa often smoke little or may not have smoked for a few days because of ill-health and the word ‘current’ is open to interpretation (particularly when translated); ‘current’ has been defined as smoking daily and non-daily in the last four weeks for the purpose of this study. Smoking habits will be further quantified at baseline interview;current alcohol usage: AUDIT, a validated tool for identifying problem alcohol behaviours [37], will be used to quantify alcohol intake. Those with an AUDIT score ≥ 8 for men or ≥ 7 for women but < 20 will be eligible for the trial.

If eligible, patients will be invited to join the trial. For those who wish to be enrolled into the trial, written informed consent will be obtained (Additional file 1).

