### Secondary outcomes

The following outcome measures will also be recorded at the six-month follow-up:sputum conversion at the end of treatment: this will be measured by negative culture or smears in the group of participants who had bacteriology confirmed PTB at baseline, i.e. cure rates in intervention group versus control group for participants who initially had sputum AFB-positive, culture-positive or GeneXpert-positive PTB;six-month continuous smoking abstinence: the Russell Standard defines continuous abstinence as a self-report of not smoking > 5 cigarettes from the start of the abstinence period (in this case, six months), supported by a negative biochemical test (exhaled carbon monoxide [CO] < 10 ppm) at final follow-up [39]. For the purpose of our study, we will, however, use a more stringent criterion of exhaled CO < 7 ppm, based on findings from our previous study that some participants who reported continued smoking had an exhaled CO < 10 ppm [26]. This analysis will be performed on the group of participants who were current tobacco smokers at baseline;reduction in harmful or hazardous drinking: alcohol use will be measured using the AUDIT questionnaire. The questionnaire will be administered at screening (which will take place on the same day or shortly after the baseline assessment) and again at three months and six months. Changes in the total AUDIT score will be used to compare change in drinking behaviour between control and intervention groups. This analysis will be performed on the group of participants who were harmful or hazardous drinkers at baseline.TB and ART medication adherence: adherence to both TB and ART medications will be measured using a modified version of the AIDS Clinical Trials Group (ACTG) Adherence Questionnaire. The questionnaire is a validated tool for measuring adherence specifically to ART and we will use an adapted version to also measure TB medication adherence [40]. Field workers will administer the baseline part of this questionnaire as part of the baseline CRF and adherence will be measured at both three months and six months.

Adherence will be measured using an adherence index calculated by the formula (using the four-day recall table):$$ \left[\mathrm{Total}\ \mathrm{number}\ \mathrm{of}\ \mathrm{doses}\ \mathrm{taken}/\mathrm{Total}\ \mathrm{number}\ \mathrm{of}\ \mathrm{doses}\ \mathrm{prescribed}\right]\ \mathrm{x}\ 100 $$

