**Fig. 2 Fig2:**
[figure not shown]
SPIRIT Figure outlining data collection throughout trial

**Table 2 Tab2:** Summary of methods of data collection and analysis for primary and secondary outcomes

Variable	Method of data collection	Method of data analysis
Primary outcome: TB treatment outcome as defined by WHO and the South Africa TB Management Guidelines (see Table 1)	• CRF and TB treatment record • Treatment outcome as recorded by TB nurses in TB cards using the standard WHO definitions of cure, completions, failure, death, TB treatment interruption, drug resistance developed in course of treatment (confirmed for correctness by checking sputum culture/smear at baseline, at 5 and 6 months)	Binary outcome: successful (cured of completed) vs not successful (died, failure, treatment interruption, drug-resistant TB) All participants, excluding those transferred out
Secondary outcome: sputum conversion	• Sputum culture/smear at baseline, 5 and 6 months to determine cure rates for PTB patients who had a positive smear or culture at baseline • Sputum conversion at 2–3 months	Binary cured vs not cured for the subgroups of participants who had a positive smear/culture at baseline Binary conversion vs not for the subgroups of participants who had a positive smear/culture at baseline
Secondary outcome: change in smoking behaviour	• CRF – questions as per Russell’s Standard – baseline smoking behaviours and then at 3 and 6 months • Exhaled carbon monoxide reading at 3 and 6 months	Binary outcome validated 3 and 6 months sustained smoking cessation for the subgroup of participants who were smoking at baseline
Secondary outcome: percentage reduction in harmful or hazardous drinking (change in AUDIT score)	• AUDIT score at baseline and at 3 and 6 months	Change in AUDIT score (continuous) for subgroups of participants who were hazardous or harmful drinkers at baseline
Secondary outcome: HIV and TB medication adherence	• CRF – questions modified from ACTG	Binary outcome (% adherent vs non-adherent)
Secondary outcome: proportion of HIV-positive participants on ART	• HIV status at baseline • ART status at baseline, 3 months and 6 months	Binary on ART vs not on ART for the subgroup of HIV-positive participants, taking into account baseline % on ART

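### Abstinence is analysed in everyone who smoked at all in the past four weeks, and smoking pattern would enter the model only if the arms happened to differ on it

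*Protocol article*

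**What the plan says.** - **Definition.** The Recruitment process section classes a patient as a current smoker by any smoking in a four-week window; the term "has been defined as smoking daily and non-daily in the last four weeks for the purpose of this study". The reason is given: "TB patients in South Africa often smoke little or may not have smoked for a few days because of ill-health", and the word is open to interpretation, particularly in translation.
- **Analysis set.** Under Secondary outcomes, for six-month continuous abstinence: "This analysis will be performed on the group of participants who were current tobacco smokers at baseline". Table 2 uses baseline smokers for both the three- and six-month results.
- **Criterion.** Abstinence is "a self-report of not smoking > 5 cigarettes from the start of the abstinence period", taken as six months, with exhaled CO below 7 ppm at final follow-up.
- **Baseline information.** Screening asks about daily, less than daily or no smoking. The same section adds: "Smoking habits will be further quantified at baseline interview". Timeline and procedures adds questions on habits and quit history. For CO, Table 2 lists "Exhaled carbon monoxide reading at 3 and 6 months".
- **Adjustment.** The Statistical analysis section adjusts for baseline characteristics and other covariates, naming HIV status, sex, alcohol/tobacco/both and district, on condition that they differ between arms at baseline. The listed subgroup analyses concern TB treatment outcomes.
- **Order of events.** The allocation envelope is drawn after the baseline interview. Randomisation is in blocks within clinic, with equal arms.

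**The concern.** A definition made wide for eligibility becomes, unrefined, the denominator of an outcome that measures stopping. Patients may have been on TB treatment for up to a month at entry, so the four-week window can reach back before treatment began. Someone who stopped at diagnosis can enrol as a current smoker and be abstinent by not restarting. A very light smoker may come close to meeting the criterion with little change, more easily over three months than six.

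Such people add abstinent participants to both arms. If the programme changes their outcome little, the difference shrinks and the odds ratio moves towards 1. Smoking pattern is also likely to predict abstinence strongly. A predictor of that kind improves precision when it is in the model even if the arms are balanced, so a rule that admits it only on observed imbalance discards the benefit. At stake is a stated objective, abstinence from smoking, which is also a step in the programme's assumed route to better TB outcomes. A diluted result could be misread as a failure of that step.

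**Working it through.** **The plan's own figure.** The only sample size stated is for TB treatment success: 0.86 vs 0.76, 80% power, 0.05 (taken as two-sided), 25% attrition. The two-proportion formula with continuity correction gives 261 per arm; 261/0.75 = 348, and 2 × 348 = 696, as stated. It does not depend on the smoking definition, and no power is claimed for abstinence.

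**Inputs for the illustration (none given in the protocol).**
- 60% of participants are baseline smokers: 0.60 × 348 = 208.8, so n = 209 per arm, with no allowance for attrition.
- Active smokers abstain at 10% (control) vs 20% (programme).
- A share f had already stopped, and a proportion q = 0.60 of them are abstinent at follow-up in both arms.

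**Formulas.**
- Arm rate: p = (1 − f) × p_active + f × q. With equal q in both arms, the difference is (1 − f) × 10 points.
- Unadjusted power: Φ[(d − 1.96 × se0)/se1], where se0 = √(2p̄(1 − p̄)/n), se1 = √([p₁(1 − p₁) + p₂(1 − p₂)]/n) and p̄ is the mean of the two rates.
- Stratified power: Φ[d/se − 1.96], where se² is the within-stratum variance weighted by stratum share, divided by n.

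**At f = 20%.**
- Rates: control 0.8 × 0.10 + 0.2 × 0.60 = 0.20; programme 0.8 × 0.20 + 0.2 × 0.60 = 0.28; d = 0.08.
- Unadjusted: se0 = √(2 × 0.24 × 0.76/209) = 0.0418; se1 = √((0.16 + 0.2016)/209) = 0.0416; power = Φ[(0.08 − 0.0819)/0.0416] = 48%.
- Stratified: se = √((0.8 × (0.09 + 0.16) + 0.2 × 2 × 0.24)/209) = √(0.296/209) = 0.0376; power = Φ(2.126 − 1.96) = 57%.
- Active smokers only: 0.8 × 209 ≈ 167 per arm, 10% vs 20%, power 73%.

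| Already stopped (f) | Rates | Odds ratio | Unadjusted | Stratified | Active smokers only |
|---|---|---|---|---|---|
| 0% | 10% vs 20% | 2.25 | 82% | – | 82% |
| 10% | 15% vs 24% | 1.79 | 64% | 70% | 78% |
| 20% | 20% vs 28% | 1.56 | 48% | 57% | 73% |

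**Wider range.** With 200 per arm and q from 0.6 to 0.8, unadjusted power goes from 80% at f = 0 to 59–62% at f = 10% and 23–25% at f = 40%.

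**The assumption that matters most.** Equal q means that the programme does nothing to prevent relapse. If it raised q from 60% to 70%, the programme rate would be 0.8 × 0.20 + 0.2 × 0.70 = 0.30 against 0.20. The difference is again 10 points, and unadjusted power with 209 per arm is about 66%.

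**What stratification does.** It leaves the 8-point difference as it is and recovers precision only. The 57% also assumes that the covariate separates the already-stopped exactly. Daily versus less than daily is a cruder marker, so its gain would probably be smaller.

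**The case against.** The strongest reply is that the wide definition is a reasoned choice in a pragmatic trial. The protocol speaks of patients who "may not have smoked for a few days because of ill-health", not of people who stopped weeks earlier. Patients who pause through illness may resume as they recover, and helping them stay abstinent is a fair target. This stands, and it is why the definition should be left alone.

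A reader might infer that people who had already stopped are credited to the programme as quitters. The protocol does not support that. Status is recorded before the envelope is drawn and allocation is equal within clinic, so they count as abstinent in the control arm too, and in expectation equally often.

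A reader might also infer that nothing at baseline tells these people apart. That is not so: frequency, habits and quit history are asked. Table 2 lists no baseline CO reading, but the assessment figure and the case report form are not shown, so one cannot be ruled out. The occasional-smoker route is narrow as well: someone smoking one cigarette a week exceeds five in six months without any change, and CO must also be below 7 ppm.

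Finally, covariates for a secondary outcome are often left to an analysis plan, and the bracketed list may not be exhaustive. That is true of which covariates are chosen. It does not answer the stated rule, under which adjustment waits for baseline imbalance; that rule governs smoking pattern even if it is meant to be on the list.

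**Conclusion.** The point holds in a limited form. The abstinence denominator can include people with little or no smoking left to stop, and the stated adjustment rule leaves a probable strong predictor unused unless the arms differ on it. The consequence is possible dilution and lost precision in a secondary outcome. It is not bias towards the programme, and the primary outcome's sample size is unaffected.

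The size cannot be established, because the share of such people, the number of smokers and the abstinence rates appear nowhere in the protocol. A fall in power from 82% to 48% is an illustration at f = 20% with no programme effect on relapse; at f = 10% the figure is 64%, and with some relapse prevention the loss is smaller. It would be wrong to read any of these as power that the trial promised and lost. The case for change rests on its low cost rather than on a demonstrated harm.

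**What to change.** 1. Keep the four-week eligibility definition and the all-smoker analysis set.
2. Include baseline smoking pattern in every three- and six-month abstinence model, whatever the observed balance. Daily versus less than daily is already asked at screening. Add recency of smoking if the baseline interview records it; the protocol does not list it.
3. Prespecify one sensitivity analysis of abstinence by baseline smoking pattern. Adjustment restores precision but not the diluted contrast, so this table is what shows whether dilution matters.

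**Cost:** one or two covariates, the first already collected, and one extra table. The sensitivity analysis has fewer participants in each group and will be less precise.
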